**Fig. 2 Fig2:**
[figure not shown]
Procedures of patient enrollment and randomization. AI = artificial intelligence, CTA = CT angiography, mRS = Modified Rankin Scale

The AI-processed image series provided suggestions for suspected intracranial aneurysms, and the radiologists could accept or reject the suggestions according to their own judgment. Both True-AI and Sham-AI can be displayed in an identical human-AI interaction platform.

Each center includes at least two participating radiologists, junior radiologists (usually attending radiologists) writing the initial report, and senior radiologists reviewing and releasing the report, which is the standard of care in China and the radiology community [25]. The participating radiologists need to meet the predefined requirements and been trained for diagnosis of intracranial aneurysms. They will assess the quality of images and data availability. In both study groups, the junior radiologists will interpret CTA images firstly without AI assistance; if aneurysms are diagnosed by junior radiologist, he/she is required to input the three-dimensional coordination of each diagnosed aneurysm in the study website.

Then the AI system act as a second reader, and will judge whether the radiologist’s diagnosis is overlapped with the AI suggestions according to the three-dimensional coordination, and only present AI suggestions that are not overlapped with radiologist’s diagnosis on the study website (the radiologist will not have access to the original AI predictions except for the presenting results). The junior radiologist will continue to independently re-assess the additional suggestions, and potentially modify his/her initial judgment accordingly, to determine his/her final report (Fig. 3). The senior radiologist has access to the first reader’s assessment and will review and release the official radiological report. They can assign cases to a consensus meeting when the radiologists find a case difficult or equivocal, where the case will be discussed at their local site for a final decision. After the diagnosis is made, the patients will be treated according to national and institutional guidelines. The requirements for participation, adherence, and protocol deviations and study monitoring are provided in the Supplementary Appendix.

**Fig. 3 Fig3:**
[figure not shown]
Schematic diagram showing how AI suggestions will be presented according to the diagnosis of junior radiologists. The workstation will judge whether there is overlap between AI suggestions and the initial diagnosis of the junior radiologists; if the two results are identical (same), no additional aneurysms will be presented on the study website; if there are no overlapped with AI suggestions (different), the additional aneurysms will be presented in the workstation. ^#^The study website will only present additional aneurysms by AI models, and they would be true-positive aneurysms or false-positive aneurysms

#### Description of the investigational product

The investigational product is a deep-learning-based intracranial aneurysm detection model: True-AI model and Sham-AI model. For both models, the full-resolution Digital Imaging and Communications in Medicine (DICOM) images are directly input without any preprocessing or rescaling. The images will be displayed in a separate web-based platform (Fig. S1 in the Supplementary Appendix).

True-AI model was developed in 16,422 CTA examinations and had a patient-level sensitivity, lesion-level sensitivity and specificity of 0.93, 0.87, and 0.79 in an independent validation dataset of 1810 cases, respectively. The Sham-AI model was developed in the same dataset with a different strategy. It was designed to have a sensitivity close to zero and a similar specificity to True-AI, so that it would not help radiologists detect additional aneurysms and expose the radiologists to the same incidental effects of the Standard-AI at the same time. Finally, Sham-AI had a patient-level sensitivity, lesion-level sensitivity, and specificity of 0.02, 0.01, and 0.80, respectively, in the same validation dataset ([name], [name], [name], [name], [name], [name], [name], [name], [name], [name], et al: Propose and validation of a placebo control for AI models in intracranial aneurysms detection: a Multi-centre, Multi-reader, Blinded Crossover Study, unpublished). We also have evaluated the influence of Sham-AI on radiologists’ diagnosis of intracranial aneurysms in a crossover, blinded diagnostic study in 28 radiologists from 7 geographically different hospitals across China, and find that radiologists had noninferior sensitivity and specificity with the aid of Sham-AI to that of reader-alone (noninferiority margin of 5%) ([name], [name], [name], [name], [name], [name], [name], [name], [name], [name], et al: Propose and validation of a placebo control for AI models in intracranial aneurysms detection: a Multi-centre, Multi-reader, Blinded Crossover Study, unpublished). The architecture of the True-AI and Sham-AI models is shown in Fig. S2 in the Supplementary Appendix.

A dedicated medical workstation (DeepWise Aneurysm Aided Detection Software, v1.0.0.2) is designed to demonstrate the DICOM images. The workstation will only present three-dimensional coordination for unoverlapped aneurysms on the study website.

### Eligibility and baseline assessment

For each included participant, the following baseline characteristics will be collected:Demographic information: gender, age, weight (kg), height (cm), education, nationality, registered residence (rural or urban), permanent address;Clinical information: Chief complaint, symptoms, indications, signs, baseline mRS;Medical history: History of intracranial aneurysms, history of head surgery, family history of SAH and intracranial aneurysms, comorbidities such as hypertension, diabetes mellitus, and cardiovascular disease;Lifestyle habits: Smoking, drinking, sleep pattern, exercise, occupation;Life quality evaluation: EuroQol 5-Dimensional, 5-Level (EQ-5D-5L) scores, sleep and psychosocial indexes (Shift Work Assessment, Pittsburgh Sleep Quality Index (PSQI), Patient Health Questionnaire-9 (PHQ-9), Hospital Anxiety and Depression Scale (HADS), Short-Form 36 Health Survey (SF-36);Information from the head CTA and report: Radiology report of head CTA, details on the number, location, size, and morphology of aneurysms, time taken for interpretation, PHASES score [26], and ELAPSS score [27] for unruptured and untreated aneurysms;Others: AI interpretation results, time of Workstation manipulation.

### Reference standard establishment

The reference standard for all CTA examinations will be determined by the Core Image Center, consisting of board-certified neuroradiologists and neurointerventional physicians at 5 large academic tertiary care hospitals with 6–15 years of working experience. Their responsibilities include determining the presence of aneurysm (location and size), intracranial arterial stenosis (≥ 50%) (location and degree of stenosis), occlusion (location), and the presence of intracranial tumors (yes/no). The physicians have access to all of the DICOM series, original reports, clinical history, and previous and follow-up examinations during interpretation and digital subtraction angiograms (DSA), if available, to establish the best possible reference standard for the labels. Each case was labeled and independently checked by two physicians. If the results were consistent, the annotation was adopted. Any disagreement was solved by discussion and consensus reading to review and check the discrepancy and make the final ground truth.

### Randomization

CTA examination will be automatically randomized within the workstation and allocated to either the intervention (True-AI) or control (Sham-AI) arm in a 1:1 ratio. Stratified by center, gender, and age (≤ 54 years or > 54 years) [28] with a combination of block sizes, the randomization sequence will be generated using a computer-generated random numerical series by an independent statistician. The original sequence will be stored in the randomization system database within the AI workstation at each site. If a subject fulfills the enrolment criteria, the enrolled cases will be assigned with a sequence and allocated to one of the groups. The sequence will not be accessible to investigators or study coordinators.

### Blinding

Study participants, local staff members obtaining patients’ consent and radiographers acquiring head CTA exams will be blinded to the randomization process, as it is automatically performed after the examination has been acquired. For radiologists interpreting head CTA exams, because junior radiologists read it firstly without AI augmentation, and AI act as a second reader and only present additional aneurysms according to junior radiologists’ initial diagnosis (Fig. 3), it is challenging for them to distinguish True-AI or Sham-AI in daily practice. Besides, randomization is conducted within the workstation automatically, resembling a “black box”, and participants have no access to the process. Finally, by ensuring that the users of a decision support system feel accountable for their own decisions can also help decrease automation bias [29]. For senior radiologists, they will review and check reports from junior radiologists and have access to the same presentation as the junior radiologists; therefore, they are also blinded to AI distribution.

Bang’s blinding index will be used to evaluate the quality of blinding for the radiologists during the trial [30].

### Plan and methods of follow-up

The participants will be contacted by the WeChat Mini Program or telephone at 3 months and 12 months by a trained team specialized in follow-up. To promote participant retention and complete high-quality follow-up, regular communication with the patients will be conducted. The local staff members will establish effective channels in the invitation by WeChat Mini Program. For nonresponders, the staff will try to contact the participant again 3 days later. The participants’ visit and evaluation schedule is shown in Table 1.

### Outcomes

#### Primary outcomes

When the enrollment is finished, the true-positive, false-positive, true-negative, and false-negative diagnosed aneurysms will be derived from the released reports against the reference standards. The primary outcome measures are coprimary endpoints of superiority in patient-level sensitivity and noninferiority in specificity (with a noninferiority margin of 5% [31]) for the True-AI arm to the Sham-AI arm in intracranial aneurysms. The patient-level sensitivity is defined as the proportion of patients with true-positive diagnosed aneurysms among patients with positive reference standards. The specificity is defined as the proportion of patients with true-negative aneurysms among patients with negative reference standards.

#### Secondary outcomes (Table S1)

Differences of other diagnostic performance metrics for intracranial aneurysms between True-AI and Sham-AI group, including accuracy, lesion-level sensitivity, positive predictive value (PPV), and negative predictive value (NPV).Differences of the diagnostic performances for other intracranial lesions between True-AI and Sham-AI group, including patient-level sensitivity, specificity, accuracy, PPV, and NPV for intracranial arterial stenosis (≥ 50%), occlusion, and intracranial tumors.Differences of the detection rates of intracranial lesions according to radiology reports between True-AI and Sham-AI group, including intracranial aneurysms, intracranial arterial stenosis (≥ 50%), occlusion, and intracranial tumors.Differences of the workload of head CTA interpretation between True-AI and Sham-AI group, including the time (seconds) of interpreting head CTA images and the number of consensus meetings (times).Differences in the proportion of participants with resource use between True-AI and Sham-AI group, including the number of care encounters (in person) during follow-up, the number of care encounters (in person) for aneurysms during follow-up, and the total number of cerebral artery tests (including DSA, CTA, MRA, and high-resolution vessel wall MR imaging) at the 3-month and 12-month follow-ups.Differences in the proportion of participants with treatment-related clinical events between True-AI and Sham-AI group including clinical follow-up, hospitalization (number of subsequent hospitalizations, number of hospitalization for intracranial aneurysms, in-hospital mortality rate, morbidity with modified RS ≥ 3 due to intracranial hemorrhage or treatment, length of hospital stay), patients undergoing DSA (detection rate of intracranial aneurysms among DSAs, detection rate of no abnormality among DSAs), patients with different methods for aneurysm treatment (conservative/coil/clip/others), patients with aneurysm treatment-related complications (intraoperative rupture, death, stroke, etc.), patients with recurrence or residual intracranial aneurysm after surgery at the 3-month and 12-month follow-up.Differences of life quality evaluation between True-AI and Sham-AI group including EQ-5D-5L scores, sleep and psychosocial indexes (shift work assessment, PSQI, PHQ-9, HADS, SF-36, mRS) at both the 3-month and 12-month follow-up assessments.Differences in the proportion of participants with outcomes of aneurysm-related events between True-AI and Sham-AI group including all-cause mortality, mortality of aneurysm rupture, aneurysm growth, aneurysm rupture, SAH, and stroke (hemorrhagic stroke, ischemic stroke) at the 3-month and 12-month follow-ups.Differences in the incremental cost-effectiveness ratio (ICER) between True-AI and Sham-AI group at 3-month and 12-month follow-up. We will calculate quality-adjusted life years (QALYs) by using the EQ-5D-5L life quality questionnaire at the 3-month and 12-month follow-up for the True-AI and Sham-AI arms. Healthcare costs per patient will be calculated as the sum of inpatient, outpatient, testing, and pharmaceutical costs during the follow-up period for the two arms. We will divide the difference in healthcare costs by the difference in QALYs to calculate the ICER of the True-AI arm compared to the Sham-AI arm. To determine whether the True-AI arm is cost-effective, we will use cost-effectiveness thresholds with an ICER < $38,070 per QALY gained will be considered cost-effective (Highly cost-effective was defined as an ICER less than 1 time the per capita gross domestic product (GDP) in China; cost-effective, an ICER of 1 to 3 times the per capita GDP; and not cost-effective, an ICER greater than 3 times the per capita GDP [32]. The per capita GDP in China in 2023 was US $ 12,690). We will conduct deterministic sensitivity analysis on all QALYs and cost parameters, typically by one-way or two-way sensitivity analyses. One-way sensitivity analysis involves systematically varying individual parameters through plausible values while holding all other values constant and assessing the impact of these individual variations, while two-way sensitivity analysis involves varying two parameters simultaneously. Our sensitivity analysis will address the uncertainty in the estimation of QALYs and cost parameters and assess its impact on cost-effectiveness results.

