A sample size iteration was processed from 5784, and the power for coprimary endpoints was 0.742 (0.80*0.928). When the sample size reached 6450, with 774 patients with intracranial aneurysms and 5676 patients without intracranial aneurysms, the power for superiority of sensitivity was determined to be 0.841, and the power for noninferiority of specificity was 0.951. Then, the power for coprimary endpoints was 0.800 (0.841*0.951) (Fig. 4). Therefore, a total sample size of 6450 is finally determined.

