#### Data analysis plan

The intention-to-treat (ITT) population will include all patients who are randomized while exclude those who withdrew consent; modified ITT (mITT) population will exclude those whose CTA are not interpreted by the study radiologists, and those with the corresponding AI process failing, and those who withdrew consent; while the Per-protocol (PP) population will only include patients who receive the randomized treatment and do not exhibit major protocol violations, excluding (1) those who withdrew consent; (2) those whose CTA are not interpreted by the study radiologists; (3) those with the corresponding AI process failing; (4) those with the participating radiologists chose not to review AI suggestions, which will be recorded by the background record.

The hypothesis of the study is that the patient-level sensitivity in the intervention arm is superior to that in the control arm, and the patient-level specificity is noninferiority, with a noninferiority margin of 5%. A comparison between the experimental group and the control group for the two primary outcomes will be conducted using the chi-square test or Fisher’s exact test. The results will include the *p* value (2-sided) and the ratio of patient-level sensitivity and specificity. The primary analysis will be based on the ITT population.

Continuous variables will be reported as the means with standard deviations (SDs) or medians with interquartile ranges (IQRs), depending on their distributions. Categorical variables will be presented as numbers and percentages. Statistical significance was set at *p* < 0.05. A 95% CI will be calculated using the Clopper-Pearson method.

The following subgroups will be included:Centers (25 centers), provinces (10 provinces), geographical areas and physician working experiences (working experiences of < 10 years vs. ≥ 10 years) and physician level (junior radiologists vs senior radiologists).Size (< 5 mm vs. ≥ 5 mm) and locations of intracranial aneurysms (anterior vs posterior, internal carotid artery vs. middle cerebral artery vs. anterior cerebral artery vs. posterior communication artery vs. anterior communication artery vs. vertebral basilar artery vs. others).Gender of patients (male vs. female), age (≤ 54 years or. > 54 years), SAH status (with vs. without SAH).History of head DSA or surgery (yes vs. no).Subsequent head DSA or surgery (yes vs. no).

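### QALYs and the ICER are built from EQ-5D-5L at 3 and 12 months only, leaving out the baseline EQ-5D-5L score that the trial also collects

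*Protocol article*

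**What the plan says.** Under Secondary outcomes, the protocol article lists "Differences of life quality evaluation between True-AI and Sham-AI group including EQ-5D-5L scores, sleep and psychosocial indexes" (shift work assessment, PSQI, PHQ-9, HADS, SF-36 and mRS), measured "at both the 3-month and 12-month follow-up assessments".

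The same section sets out the cost-effectiveness method. QALYs are calculated per arm from the EQ-5D-5L questionnaire at the 3-month and 12-month follow-up. The ICER is the difference in healthcare costs divided by the difference in QALYs, reported at 3 and at 12 months. No baseline value and no adjustment appear in that rule.

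Under Eligibility and baseline assessment, the baseline data include "Life quality evaluation: EuroQol 5-Dimensional, 5-Level (EQ-5D-5L) scores, sleep and psychosocial indexes", naming the same instruments. mRS is also recorded: "Chief complaint, symptoms, indications, signs, baseline mRS".

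The Data analysis plan says "Continuous variables will be reported as the means with standard deviations (SDs) or medians with interquartile ranges (IQRs), depending on their distributions". The only between-arm test it names is tied to the primary endpoints: the comparison "for the two primary outcomes will be conducted using the chi-square test or Fisher’s exact test". For missing baseline characteristics, the article says that the data are marked NA and left out of the analysis.

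**The concern.** A QALY is an area under the utility curve over time, and that curve starts at baseline. If only the 3- and 12-month scores enter, the 3-month QALY rests on a single utility value, and the first quarter of the 12-month horizon has no starting point. Any chance difference between arms in baseline utility that persists to follow-up then appears as a QALY difference.

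This matters more for a ratio than for a mean difference. The ICER divides by the QALY difference, which is expected to be very small here because few patients get a different report. A small chance shift in the denominator can change the ratio greatly, or change its sign. The result is then judged against a fixed threshold per QALY.

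The other quality-of-life and psychosocial scores raise a weaker version of the point. Their baseline values are in hand and would improve precision, but the article does not say whether they will be used. The Discussion asks whether extra detection causes anxiety and depression, so a tight interval on these scores is useful even if the result is null.

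**Working it through.** 1. **The plan's own figures.** The cost-effectiveness threshold reproduces: 3 × 12,690 = 38,070 US dollars per QALY. The size and power also agree: "Therefore, a total sample size of 6450 is finally determined", with 0.12 × 6,450 = 774 aneurysm patients and 0.841 × 0.951 = 0.800. The article gives no SD, effect size, correlation or power for the quality-of-life scores or QALYs, so there is no figure of that kind to reproduce.

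2. **Weight of the baseline value in a QALY.** Assume linear interpolation between utilities u0, u3 and u12.
   - 3-month QALY = 0.25 × (u0 + u3)/2 = 0.125 u0 + 0.125 u3. Baseline carries half the weight.
   - 12-month QALY = 0.25 × (u0 + u3)/2 + 0.75 × (u3 + u12)/2 = 0.125 u0 + 0.5 u3 + 0.375 u12. Baseline carries one eighth.

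3. **Size of a chance baseline imbalance.** With 5% attrition, n per arm = 6,450 × 0.95 / 2 ≈ 3,064. The SE of the baseline difference is √(2/3,064) = 0.026 SD, a 95% range of about ±0.05 SD. With correlation r and equal SDs over time, a share r of it carries into the follow-up difference. At the limit of that range this is 0.015 SD (r = 0.3), 0.025 SD (r = 0.5) or 0.035 SD (r = 0.7).

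4. **Adding baseline to the QALY is not enough on its own.** For the 12-month QALY in step 2, the share carried is 0.125 + 0.875 r. That is 0.3875, 0.5625 and 0.7375 for r = 0.3, 0.5 and 0.7, or about 0.019, 0.028 and 0.037 SD. Without regression on baseline, the imbalance passes through slightly more, not less.

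5. **Precision gain from baseline adjustment.** Variance factor = 1 − r²; CI width factor = √(1 − r²). The minimum detectable difference (MDD; two-sided 5%, 80% power) is (1.960 + 0.842) × √(2(1 − r²)/3,064) SD.

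| r (assumed) | Variance factor | CI width falls by | Equivalent N | MDD (SD) |
|---|---|---|---|---|
| not adjusted | 1.00 | – | 1.00 | 0.072 |
| 0.3 | 0.91 | 4.6% | 1.10 | 0.068 |
| 0.5 | 0.75 | 13.4% | 1.33 | 0.062 |
| 0.7 | 0.51 | 28.6% | 1.96 | 0.051 |

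   With 30% loss to follow-up (assumed), the MDD is 0.083 SD unadjusted and 0.080, 0.072 and 0.060 SD adjusted. Plain change scores are no substitute: their variance factor is 2(1 − r), which is 1.4 at r = 0.3 and exceeds 1 whenever r is below 0.5.

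6. **Dilution.** From the plan's sensitivities, specificities and prevalence, the net difference in positive reports is 0.12 × (0.75 − 0.65) + 0.88 × (0.90 − 0.88) = 0.012 + 0.0176 = 0.0296, a dilution of 1/0.0296 ≈ 34-fold. An illustrative shift of 0.5 SD in those patients moves the arm mean by 0.5 × 0.0296 ≈ 0.015 SD. The carried imbalance in step 3 is as large or larger. To reach the MDD, the shift per affected patient would have to be about 34 × 0.072 ≈ 2.4 SD unadjusted, and still about 34 × 0.051 ≈ 1.7 SD at r = 0.7.

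**The case against.** The strongest objection is that this is a condensed article, and that covariates for secondary outcomes usually sit in the analysis plan, which is not shown. For the quality-of-life scores this stands. A reader might infer that the scores will be compared at follow-up without using baseline. The documents do not say so. The outcome is worded as a between-arm difference at 3 and 12 months, which is also what a baseline-adjusted model estimates. The sentence on means and medians is a reporting convention, and the chi-square or Fisher test is named for the primary outcomes only. Collecting the instruments at baseline fits planned adjustment at least as well as its absence.

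For QALYs the objection is weaker, because there the article does state a method: which questionnaires are used and which difference is divided into which. An unseen plan may add the baseline value, but the text as it stands leaves it out. The planned one-way and two-way sensitivity analyses vary QALY and cost parameters over plausible ranges. They do not remove a baseline imbalance from the base-case estimate.

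A reader might also infer that precision decides whether an effect on anxiety or quality of life can be seen. The figures do not support that. Dilution is the main limit, and even the most favourable assumed correlation leaves an implausibly large effect per affected patient.

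It also stands that randomisation makes the unadjusted difference unbiased on average, that the correlations are assumed, and that a linear model is not an obvious choice for mRS, which is ordinal and restricted to 3 or below at entry.

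**Conclusion.** The point holds for QALYs and the ICER. The stated rule omits a baseline utility that the trial collects. That value would carry half the weight of a 3-month QALY and one eighth of a 12-month QALY under linear interpolation. Chance imbalance of up to about 0.05 SD at baseline can pass 0.015 to 0.035 SD into follow-up utility, for an assumed r of 0.3 to 0.7 and 5% attrition. That is at least as large as the illustrative effect on the arm mean.

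For the other scores, the point is a request to fix baseline adjustment in writing, not a demonstrated fault. If they were left unadjusted, the precision forgone would be 9 to 49% of the variance under the same assumed range.

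The matter concerns secondary outcomes only. It leaves the co-primary analysis and the sample size untouched. It is worth doing because the data are already collected, not because it would make the effect detectable.

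**What to change.** - Compute QALYs from EQ-5D-5L at baseline, 3 and 12 months, and state the interpolation rule.
- Estimate the between-arm QALY difference, which is the ICER denominator, by regression on arm, baseline EQ-5D-5L and the randomisation strata (centre, gender, age group). The two steps belong together, as step 4 of the working shows.
- Apply the same adjustment to EQ-5D-5L, PSQI, PHQ-9, HADS and SF-36 at 3 and 12 months, by ANCOVA or a mixed model over both visits. Use an ordinal model with baseline mRS for mRS.
- Keep patients whose baseline score is missing, by mean imputation or a missing indicator, both acceptable for a baseline covariate in a randomised comparison. State that the rule marking missing baseline data as NA does not remove these patients.
- Confirm that the baseline questionnaires are completed before the patient learns the CTA result, since the baseline list also contains items from the report.

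The cost is a few sentences in the protocol and analysis plan, with no new data and no change to the sample size.

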In addition, we chose intracranial aneurysms as the target lesion not only because of the challenges of diagnosis but also because of continued uncertainty regarding the optimal management of unruptured intracranial aneurysms (preventive aneurysm repair versus observation) [4]. This paradox would be exacerbated by increasing the detection rate of unruptured aneurysms by the introduction of AI models, especially small aneurysms. It is not clear whether more detected unruptured intracranial aneurysms, assisted by AI technology, would favor patient prognosis, and whether increased detection would increase unnecessary preventive aneurysm repair, or false-positive and small or tiny aneurysms cause patient anxiety and depression in downstream management. Therefore, the target patients are those with mRS ≤ 3 who can participant in questionnaire inquiry and unlikely harboring ruptured aneurysms, to explore the impact of AI on intracranial aneurysms, and highlight the real-world influence of AI on clinical practice, especially in the field of interpretation of medical images.

We plan to enrol 6450 participants in more than 10 provinces across China to represent the influence of AI in clinical practice at a national level. The study is the first prospective double-blinded RCT of AI in radiology and will provide the highest-level evidence for the application of AI systems in clinical settings, not limited to intracranial aneurysms. It is highly expected that the study may set a typical paradigm for AI studies in the radiology field.

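### The cost-effectiveness verdict is taken at 3 and 12 months, before most benefit from preventing rupture could appear, so it depends heavily on the horizon and on chance

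*Protocol article*

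**What the plan says.** All of the following is in the protocol article, Secondary outcomes (Table S1), unless another section is named.

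- **Horizon:** the outcome is "Differences in the incremental cost-effectiveness ratio (ICER) between True-AI and Sham-AI group at 3-month and 12-month follow-up". The SPIRIT-AI schedule and the follow-up section both end at 12 months.
- **QALYs:** calculated "by using the EQ-5D-5L life quality questionnaire at the 3-month and 12-month follow-up".
- **Costs:** the "sum of inpatient, outpatient, testing, and pharmaceutical costs during the follow-up period".
- **Decision rule:** "we will use cost-effectiveness thresholds with an ICER < $38,070 per QALY gained will be considered cost-effective". The threshold is three times per capita GDP, and the GDP figure is stated: "The per capita GDP in China in 2023 was US $ 12,690".
- **Sensitivity analysis:** "We will conduct deterministic sensitivity analysis on all QALYs and cost parameters, typically by one-way or two-way sensitivity analyses". The horizon is not among the quantities varied.
- **Population and expected harms (Discussion):** participants are described as unlikely to carry ruptured aneurysms. The authors leave open "whether increased detection would increase unnecessary preventive aneurysm repair" and whether false-positive or tiny findings cause anxiety and depression.

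**The concern.** Finding an unruptured aneurysm can lead to angiography, repair, complications and worry within months. The gain is a rupture that does not happen, and that gain is spread over the years that follow. A ratio closed at 3 or 12 months can include the early costs and harms but only a sliver of the gain.

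The article does more than report this ratio. It uses the ratio to classify the technology as cost-effective or not. The Introduction says the trial is meant to support clinical deployment of AI systems, so a published label in either direction would be read as a judgement of value. The planned sensitivity analyses would not expose the problem, because they leave the horizon fixed.

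**Working it through.** **Threshold.** 3 x 12,690 = 38,070, so the stated figure is reproduced exactly.

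**Extra findings in the True-AI arm.** Inputs are from Sample size calculation: 6450 patients at 1:1, prevalence 12%, sensitivity 0.65 versus 0.75, specificity 0.90 versus 0.88.
- Patients per arm: 6450 / 2 = 3225.
- Extra true positives: 3225 x 0.12 x 0.10 = 387 x 0.10 = 38.7.
- Extra false positives: 3225 x 0.88 x 0.02 = 2838 x 0.02 = 56.8.

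**Upper bound on rupture-prevention benefit within the window.** The documents give no rupture risk, so r = 0.1-5% per year is assumed. Each remaining choice favours the AI: every extra case is an unruptured aneurysm repaired on day 0, repair is perfect and harmless, and every averted rupture counts as a death avoided with full health until the horizon H (in years). With ruptures spread evenly over time:

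QALY per extra true positive = r x H x H/2. This is 0.5r at 12 months and 0.03125r at 3 months.

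Allowed net extra cost = QALY x $38,070.

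The 20-year column integrates r e^(-rt) (e^(-0.05t) - e^(-0.05 x 20)) / 0.05 over 0 to 20 years. The 20-year horizon and the 5% discount rate are both assumptions.

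| r per year | QALY, whole arm, 12 months | Allowed per extra aneurysm patient, 3 months | 12 months | 20 years | 20 years / 12 months |
|---|---|---|---|---|---|
| 0.1% | 0.019 | $1.2 | $19 | $4,000 | 210 |
| 0.5% | 0.097 | $5.9 | $95 | $19,522 | 205 |
| 1% | 0.19 | $11.9 | $190 | $37,904 | 199 |
| 5% | 0.97 | $59.5 | $952 | $152,118 | 160 |

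Ruptures averted in the arm over 12 months: 38.7 x r = 0.04 to 1.9. The total allowed at 12 months is $737 to $36,833, which must also cover work-up of the false positives. Spread over all 38.7 + 56.8 extra positives, it is about $8 to $386 each.

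**Noise in the denominator.** The 12-month QALY SD is assumed to be 0.05-0.20, with 5% attrition.
- SE = SD x sqrt(2 / (3225 x 0.95)) = 0.0013 to 0.0051.
- 95% half-width = 1.96 x SE = 0.0025 to 0.010 per patient.
- Maximum gain at r = 1%: 0.1935 / 3225 = 0.00006 per patient. The half-width is about 42 to 167 times this.
- At r = 5% the maximum is 0.0003, and the half-width is still about 8 to 33 times this.

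**Illustration of the observed verdict.** Assume $5,000 per extra true positive, $500 per extra false positive, r = 1%, and costs measured without sampling error.
- Extra cost per patient: (38.7 x 5,000 + 56.76 x 500) / 3225 = $68.8.
- Expected 12-month ICER: 68.8 / 0.00006, about $1.1 million per QALY.
- Chance that observed net benefit is nevertheless positive: Phi((0.00006 x 38,070 - 68.8) / (SE x 38,070)) = 0.09 for SD 0.05 and 0.37 for SD 0.20.

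**The case against.** The strongest defence is that this is a within-trial evaluation. The stated outcome is the ICER at two visits with costs to those visits, the schedule ends at 12 months, and no lifetime claim is made. That stands as far as the description goes: within-trial costs and QALYs are a legitimate secondary outcome. It does not cover the classification, because the rule is introduced as the way to determine whether the True-AI arm is cost-effective, without any limit to the trial period.

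A reader might go further in four ways that the documents do not support.

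- **That the horizon alone settles the verdict.** No unit cost of work-up or repair is given. The expected verdict changes with the horizon only if net cost per extra aneurysm patient lies between the 12-month and long-term break-even values. That interval is wide ($190 to $37,904 at 1% per year), but it cannot be checked. The observed verdict could also fall on either side by chance.
- **That the window captures nearly all of the cost.** The secondary outcomes list conservative management beside coil and clip, and the Discussion describes unresolved uncertainty between repair and observation. Surveillance of observed patients can continue past 12 months, so some cost is cut off too.
- **That the figures cap all possible benefit.** SAH is not an exclusion criterion, and a subgroup with and without SAH is planned. A ruptured aneurysm found through the AI could bring benefit inside the window. The bound covers unruptured aneurysms only.
- **That allowed cost grows with the square of the horizon, 400-fold at 20 years.** This needs r x H to be small. At 5% per year the undiscounted gain is 20 - (1 - e^(-1))/0.05 = 7.36 QALYs, against 0.0246 at one year, or about 300-fold. With 5% discounting the range is 160-210.

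It is also fair to say that a full long-horizon model is partly a question of scope and could sit in a health-economic plan that is not shown. The absence of such a model is therefore not the fault. The fault is the verdict attached to the short horizons.

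**Conclusion.** The point holds in a limited form. The article fixes the horizon, the cost window and the decision rule, and together they can mislead. Under assumptions that favour the AI, the rule leaves room for only about $19-$952 of net cost per extra aneurysm patient found at 12 months and $1-$60 at 3 months. The same detection gain would justify roughly 160-210 times the 12-month sum over 20 years. The expected verdict therefore depends heavily on the horizon. The observed verdict depends largely on random variation in a QALY difference close to zero.

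A result of not cost-effective is the likelier direction, but it is not certain. The conclusion rests on assumed rupture risks, QALY SDs, discounting and a 20-year comparison horizon, none of which is in the documents. It also rests on the extra aneurysms being mostly unruptured, as the Discussion expects.

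The coprimary endpoints, the sample size and data collection are not affected.

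**What to change.** 1. Report costs and QALYs at 3 and 12 months as descriptive within-trial results, with uncertainty intervals for the cost difference and the QALY difference.
2. Remove the cost-effective / not cost-effective classification at those horizons. Alternatively, limit it explicitly to a within-trial statement that does not bear on long-term value.
3. If a threshold verdict is wanted, base it on a pre-specified, discounted long-horizon model. It should use the trial's own sensitivity, specificity, treatment uptake, complications and costs, state its sources for rupture risk and treatment effect, and vary rupture risk and horizon in sensitivity analysis.

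Steps 1 and 2 cost only protocol or analysis-plan wording. Step 3 is optional and needs modelling work but no new patient data. The price is that the trial itself yields no headline cost-effectiveness verdict, and any long-term conclusion rests on modelled inputs.
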